### Interim analyses {21b}

Interim analysis of the obtained follow-up data will be available by 12 months postoperatively for at least 20 patients in each cohort. The criteria for study termination include the following: (1) the number of repeated surgeries in any group exceeds 50%, (2) any group demonstrates a higher frequency of negative neurological postoperative outcomes and/or significant decline of ODI level compared to baseline by at least 10 points, and (3) the number of postoperative complications exceeding 50% in any group.

An interim analysis will be performed by an investigator not involved in patient treatment ([name], MD, PhD).

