#### Sample size {14}

Following a non-inferiority study design, we calculated the sample size based on the primary outcome. According to the most recent randomized trial [6], the standard deviation for the ODI in the fusion group is 20 points. With a non-inferiority margin of δ = 12, two-sided α-level of 0.05, power of 80%, and 1:1 allocation ratio, the required sample size is 70 patients. Considering the potential of 20% of patients missing the obligatory follow-up procedures, we plan to include at least 86 patients (43 patients per group).

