## Statistical methods

### Statistical methods for primary and secondary outcomes {20a}

The results will be analysed using the intention-to-treat principle. Statistical significance will be defined as *p* < 0.05 based on a two-sided test. No adjustments for multiple tests are planned. The normality of variables will be evaluated using the Shapiro-Wilk statistic. Student’s *t*-test (for normally distributed data) and Pearson’s chi-square test (for categorical data) will be used to reveal differences in symptom rates among the groups. Multiple linear regression will be used to measure point estimates and confidence intervals for group differences in the ODI and clinical scale scores from baseline to the 2-year follow-up.

The non-parametric Mann-Whitney *U* test will be used to reveal differences in continuous variables between groups both pre- and postoperatively. Continuous data within the groups will be compared using the Wilcoxon test. Categorical parameters among the groups will be compared using Fisher’s exact two-tailed test.

Complication incidence during the 2-year follow-up will be compared between groups using Kaplan–Meier survival curves and the log-rank test. The significance of the risk factors (predictors) for all registered complications will be evaluated using univariate and multivariate logistic regression models.

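### The interim limits on repeat surgery and complications look at one arm at a time, so 10/20 against 0/20 repeat surgeries or non-neurological complications meets no written criterion

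*Protocol article*

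**What the plan says.** All references are to the protocol article.

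*Interim analyses {21b}* places the look when follow-up data are "available by 12 months postoperatively for at least 20 patients in each cohort". It then lists three termination criteria:

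1. Repeat surgery: "the number of repeated surgeries in any group exceeds 50" per cent.
2. Neurological outcome and ODI: "any group demonstrates a higher frequency of negative neurological postoperative outcomes and/or significant decline of ODI level compared to baseline by at least 10 points".
3. Complications: "the number of postoperative complications exceeding 50% in any group".

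Criteria 1 and 3 are limits within a single arm. Only criterion 2 has comparative wording, and it gives no size or test for the difference. The section gives no expected event rate and no basis for the 50% figure.

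*Statistical methods {20a}* does compare complications between arms: "Complication incidence during the 2-year follow-up will be compared between groups using Kaplan–Meier survival curves and the log-rank test". That comparison is not linked to stopping or to any interim review. The same section names a test for two-by-two tables: "Categorical parameters among the groups will be compared using Fisher’s exact two-tailed test". The significance level there is two-sided 0.05.

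**The concern.** The trial exists to compare two operations, and the Discussion expects that they may differ in complication rates. A harm rule that looks at each arm alone responds to the overall level of events, not to an excess in one arm. If half the patients in one arm and none in the other had repeat surgery, criteria 1 and 3 would both be silent. A report that no stopping criterion was met would then be accurate, yet would say nothing about the imbalance.

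There is also a counting problem. Both criteria speak of a number of surgeries or complications but express it as a percentage, without saying of what. Several minor events in a few patients could reach the limit on one reading and not on another.

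**Working it through.** **No figure to reproduce.** The protocol gives no error rate or derivation for the 50% limits, so the check is of how the rule behaves.

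**Inputs from the protocol article.** Interim size: at least 20 per arm (*Interim analyses*). Limit: more than 50% in one arm (same section). Test and level: Fisher's exact, two-sided 0.05 (*Statistical methods*). Planned size: 43 per arm (*Sample size*). The true event rates below are assumptions.

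**Step 1: what triggers.** More than 50% of 20 means at least 11. Since 10/20 is exactly 50%, it does not trigger. This holds whether the ten are patients or procedures, provided the denominator is the 20 patients in the arm.

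**Step 2: how extreme 10/20 against 0/20 is.** Fisher's two-sided p = 2 × C(20,10)/C(40,10) = 0.0004. Smaller imbalances also reach 0.05: 10/20 against 3/20 gives p = 0.041, and 5/20 against 0/20 gives p = 0.047.

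**Step 3: chance that one arm exceeds the limit, each patient counted once.** P(X ≥ 11), X ~ Binomial(20, π):

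| True rate π | P(X ≥ 11 of 20) |
|---|---|
| 20% | 0.0006 |
| 30% | 0.017 |
| 40% | 0.128 |
| 50% | 0.412 |
| 60% | 0.755 |

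The other arm's rate does not enter. A larger interim sample does not help below 50%: with 43 per arm (at least 22 needed), the probability is 0.003 at a true 30% and 0.091 at 40%.

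**Step 4: the between-arm comparison.** Summing over all pairs of independent binomial counts with 20 per arm:

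| True rates | Written limit exceeded in either arm | Fisher p < 0.05, excess in the worse arm |
|---|---|---|
| 30% v 5% | 0.017 | 0.45 |
| 40% v 5% | 0.128 | 0.72 |
| 40% v 10% | 0.128 | 0.49 |
| 50% v 5% | 0.41 | 0.89 |

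With both arms at a true 40%, where there is no excess at all, the written limit is exceeded in at least one arm with probability 1 − (1 − 0.1275)² = 0.24. That is higher than for 40% against 5%.

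**Step 5: counting events instead of patients.** As an illustration, assume Poisson events per patient with the same chance π of at least one. The mean over 20 patients is −20 ln(1 − π). At π = 40% this is 10.2, and P(at least 11 events) = 0.44 instead of 0.13. At 30% it is 0.11 instead of 0.017; at 50%, 0.82 instead of 0.41. The rule's behaviour therefore depends heavily on a definition that the protocol does not give.

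**Step 6: false flags.** With equal true rates and 20 per arm, the chance that Fisher's two-sided p falls below 0.05 is at most 0.025 over all common rates, because the exact test is conservative.

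**The case against.** The strongest reply is that the criteria should be read together. Criterion 2 is comparative for neurological outcomes, and neurological deterioration is among the adverse events to be analysed. A reader might infer from criteria 1 and 3 that any large one-sided harm would be missed. The text does not support that: if the ten events were neurological, criterion 2 could apply. The point is confined to repeat surgery and non-neurological complications such as infection or implant failure.

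A reader might also infer that the limits almost never fire when an arm is harmful. That does not hold either. With each patient counted once, the probability is 0.41 at a true 50% and 0.76 at 60%, and it is higher if events are counted.

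Third, Step 4 is not like for like. The written limits are grounds for ending the trial, whereas the Fisher comparison would only prompt a review and should be the more sensitive of the two. An absolute limit against a catastrophic rate is a legitimate choice. This stands, and the comparison does not show the 50% limits to be wrong; it shows that nothing else covers what they leave open.

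Finally, there is other oversight. The list of criteria is not stated to be exhaustive, adverse events go to the chief investigator, audits involving the ethics board take place every 20 inclusions, and an observer described as independent runs the interim analysis. The article may also condense a fuller document. But none of these passages sets a comparative threshold for the events in question. The point concerns how the published criteria behave, not a missing detail.

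**Conclusion.** The point holds within those bounds. Criteria 1 and 3 can stay silent on a gross one-sided excess of repeat surgery or non-neurological complications, and no other passage ties a comparison of these events to stopping or review.

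The size depends on assumed true rates and on counting each patient once. The gap is widest at true rates of about 30% to 40% in the worse arm, where the limit is exceeded with probability 0.017 to 0.13. It narrows as the true rate rises past 50%. The 10/20 against 0/20 example needs no assumed rate, only that the events are non-neurological and that the ODI part of criterion 2 is not met. This is a weakness in safety monitoring that should be corrected. It does not affect the primary ODI analysis.

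**What to change.** In *Interim analyses {21b}*:

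- Define criteria 1 and 3 as the proportion of patients in the arm with at least one repeat surgery, or at least one postoperative complication, and state the denominator.
- At the existing look, tabulate both outcomes by arm and compare them with Fisher's exact test, which the protocol already names. State in advance the level at which an excess triggers a formal review of whether to continue. The trigger is for a review, not an automatic stop.
- The absolute limits may stay as the sponsor's choice. If they do, state the event rate the sponsor expects and how the limit follows from it.

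The cost is a wording change and one two-by-two table per criterion at a look already planned. At a two-sided 0.05 level with 20 per arm, the chance of an unnecessary review under equal rates is at most about 2.5% per criterion. No alpha is spent on the ODI endpoint.

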**Methods:**

This study is focused on the non-inferior clinical results of decompression compared with the standard fusion procedure. In the decompression group, the spinous process, the interspinous and supraspinous ligaments, part of the facet joints, and corresponding parts of the vertebral arch are to be preserved intact. In the fusion group, decompression is to be supplemented with transforaminal interbody fusion. Participants meeting the inclusion criteria will be randomly divided into two equal groups (1:1), depending on the surgical method. The final analysis will include 86 patients (43 per group). The primary endpoint is Oswestry Disability Index dynamics at the end of the 24-month follow-up compared to the baseline level. Secondary outcomes included those estimated using the SF-36 scale, EQ-5D-5L, and psychological scales. Additional parameters will include sagittal balance of the spine, fusion results, total cost of surgery, and hospital stay followed by two-year treatment. Follow-up examinations will be performed at 3, 6, 12, and 24 months

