## Outcomes {12}

### Primary endpoint

The primary endpoint includes the dynamics of ODI parameters at the end of the 24-month follow-up compared to the baseline level [7]. This patient-reported measurement precisely estimates the impairment of a participant’s quality of life resulting from low back pain and clearly reflects the clinical outcome of the treatment. Parameter assessment is to be considered at all stages of the study beginning from baseline examination, followed by a follow-up examination 2 years postoperatively. The questionnaire consists of 10 sections, comprising six statements per section. Each answer is assessed using six grades (ranging from 0 to 5) with a maximum score of 50 points per participant. Subsequently, the total score is converted into a percentage ratio (from 0 to 100%). If any of the sections are not applicable or have been withdrawn for ethical reasons, the total score is calculated within nine sections and is divided by 45.

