## Discussion

Currently, the selection of surgical solutions for lumbar stenosis remains controversial. This study was designed to provide surgeons with high-level evidence by comparing the clinical outcomes of the two most popular treatment methods. The non-inferiority study design [14] was chosen because according to the current evidence [4, 5] and our experience, both methods are non-inferior (comparable) in terms of the primary endpoint, while there may be superiority in certain secondary endpoints, such as cost effectiveness and lower complication rates.

The non-inferior margin was chosen based on the minimum clinically important difference (MCID), which represents the smallest improvement considered worthwhile by a patient. For patients with lumbar spine stenosis, the MCID in ODI score ranges from 12.54 to 12.8 points [15, 16]. Therefore, a non-inferiority margin of *δ* = 12 was selected according to this data.

To develop the structure of this study, we did our best to maximise the homogeneity of the participant groups. For this purpose, we used precise inclusion and exclusion criteria and accurately restricted the range of surgical methods and postoperative rehabilitation treatment. The key role of postoperative rehabilitation in favourable clinical outcomes is widely known. In our study, all included participants are scheduled for rehabilitation treatment at the same rehabilitation centre within 3 months postoperatively. We believe that these conditions maximise the homogeneity of the participant groups and limit possible clinical outcomes by several factors. We suggest that the mentioned structure of the study implicates decompressive intervention as the only factor for favourable clinical outcomes compared to spinal fusion.

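### The ODI limb of interim termination criterion 2 is worded in the wrong direction: a fall in ODI is improvement, so as written it triggers on benefit and never on worsening

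*Protocol article*

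**What the plan says.** Under Interim analyses {21b}, the protocol plans a look at 12-month data "for at least 20 patients in each cohort" and introduces three stopping rules with "The criteria for study termination include the following". Criterion 1 is that "the number of repeated surgeries in any group exceeds 50" per cent, and criterion 3 sets the same 50% limit for postoperative complications. Criterion 2 has two limbs joined by and/or:

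- neurological: "any group demonstrates a higher frequency of negative neurological postoperative outcomes";
- ODI: "significant decline of ODI level compared to baseline by at least 10 points".

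Three other places fix what a change in ODI means:

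- The Abstract (Methods) gives the full name of the instrument: "The primary endpoint is Oswestry Disability Index dynamics at the end of the 24-month follow-up compared to the baseline level".
- The Primary endpoint section says that the ODI "precisely estimates the impairment" of quality of life, and scores it from 0 to 100%.
- The Discussion describes the MCID as the smallest improvement worthwhile to a patient, and states that "the MCID in ODI score ranges from 12.54 to 12.8 points".

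**The concern.** On an index of disability or impairment, a fall from baseline is a benefit. The ODI limb therefore names the outcome that both operations are meant to produce, at a size below the protocol's own threshold for worthwhile improvement. Patients or arms whose ODI rises do not meet it, however large the rise.

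This is one of only three listed termination criteria, and the only one that uses the primary outcome measure. If it is applied as worded, it gives the wrong signal. If whoever runs the interim analysis silently reverses it, the rule in use is no longer the pre-specified one. That matters more in an open-label trial where one investigator performs the interim analysis.

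The neurological limb raises a lesser question. It gives no limit, minimum difference or test, although criteria 1 and 3 each state a percentage.

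**Working it through.** The protocol gives no stopping probability or error rate for criterion 2, so there is no figure of its own to reproduce. The check has three parts.

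**1. Direction.** The scale measures impairment (Primary endpoint) and is called a disability index (Abstract). Lower is therefore better, and a decline is improvement. No section states the opposite or corrects the wording of the interim rule.

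**2. ODI limb, read literally as a group mean.** Inputs:

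- n = 20 per arm (Interim analyses {21b});
- SD = 20 (Sample size {14}, where it is given for the ODI in the fusion group; assumed here to apply to change from baseline, with 15 and 25 as a range);
- true mean improvement m = 12.54 or 12.8 in both arms (Discussion). This is an illustration, because the protocol states no expected mean change.

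Formulas, with Φ the standard normal distribution function and independent arms:

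- SE = SD/√20
- P(one arm) = Φ((m − 10)/SE)
- P(at least one arm) = 1 − (1 − P(one arm))²

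For SD 20, SE = 20/√20 = 4.47:

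- m = 12.54: Φ(2.54/4.47) = Φ(0.568) = 0.715; at least one arm 1 − 0.285² = 0.919
- m = 12.8: Φ(2.8/4.47) = Φ(0.626) = 0.734; at least one arm 1 − 0.266² = 0.929

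| SD | SE | At least one arm, m = 12.54 | At least one arm, m = 12.8 |
|---|---|---|---|
| 15 | 3.35 | 0.950 | 0.959 |
| 20 | 4.47 | 0.919 | 0.929 |
| 25 | 5.59 | 0.895 | 0.905 |

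For comparison, take the limb as a mean rise of at least 10 points, with SD 20. At least one arm meets it with probability about 0.025 if the true mean change is zero, and below 0.000001 if the true improvement equals the MCID.

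The word "significant" in the ODI limb changes little. If it means a significant within-arm change, the mean fall must exceed about 2.093 × SE (t, 19 df). At SD 20 that is 2.093 × 4.47 = 9.4, already below 10. At SD 25 it is 2.093 × 5.59 = 11.7, which lowers the last row to about 0.81 to 0.82.

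**2a. The same limb, read at patient level.** The sentence can also be parsed as a higher frequency of patients with a 10-point ODI decline. With SD 20 and m = 12.54, and normality assumed, Φ(2.54/20) = 0.55 of patients fall by at least 10, and Φ(−22.54/20) = 0.13 rise by at least 10. The rule would count the first group, so the arm with more improvers would trigger it.

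**3. Neurological limb.** The protocol gives no event rates, so equal true rates p in both arms are assumed, with 20 per arm. If any difference in counts is enough, P = 1 − Σₖ Bin(k; 20, p)². If a difference must reach p < 0.05 on the two-tailed Fisher's exact test named under Statistical methods {20a}, P is the sum of Bin(i)·Bin(j) over tables with p < 0.05. With no events in one arm, that needs at least 5 in the other (p = 0.047).

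| Assumed true rate | Any difference in counts | Fisher p < 0.05 |
|---|---|---|
| 5% | 0.690 | 0.002 |
| 10% | 0.786 | 0.012 |
| 15% | 0.822 | 0.020 |

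**The case against.** The strongest reply is that every other item in the list is a harm: repeat surgery, negative neurological outcomes and complications. In that company, decline reads naturally as deterioration. This stands as to intent. A reader might infer from the probabilities above that the trial would be stopped because it is working. The documents do not support that, because anyone applying the list would see that it is meant to catch harm. Nor is it right to infer that patients have no protection against deterioration, since criteria 1 and 3 and the neurological limb remain. The reply does not rescue the wording, which speaks of the level of the score and not of function.

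A second reply is that the sentence does not say group mean, that the Discussion defines the MCID for a patient, and that no expected mean change is given. This stands against treating 0.92 to 0.93 as a forecast. It does not affect the direction, which is reversed under either reading.

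A third reply concerns the neurological limb. A reader might infer that it fires on chance in 69% to 82% of trials. That holds only if any difference in counts is enough, which the protocol does not say. The interim section does not cite Fisher's test, but it is the test the protocol names for comparing categorical parameters between groups, and it gives 0.2% to 2.0%. The comparator is also uncertain, since the reference to baseline may govern both limbs. A test or limit of this kind is detail that an article may leave to the full protocol. This limb is therefore a request for clarification, not an error. That excuse does not extend to the ODI limb, which is stated and stated wrongly.

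**Conclusion.** The ODI limb of criterion 2 is wrong as written. Its direction contradicts the protocol's own description of the scale, and its 10-point trigger lies below the protocol's own MCID for improvement. Taken literally as a group mean, it would be met by at least one arm with probability about 0.92 to 0.93 if both arms truly improved by the MCID (0.89 to 0.96 for SDs of 25 to 15). A mean worsening could not meet it. These figures rest on 20 patients per arm, normal arm means, independent arms, and the SD of 20 applying to change from baseline. The finding on direction needs none of these assumptions. It relies on the instrument's name and on the word impairment, because the protocol never says outright that higher is worse.

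This is a drafting error in a decision rule. It needs correcting because a termination rule should be executable as worded. The undefined neurological comparison is secondary, with a false-trigger probability anywhere from about 0.2% to 82% depending on the reading and the assumed event rate.

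**What to change.** In Interim analyses {21b}, the sponsor should:

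1. Reconcile the ODI limb with the scale in the Primary endpoint section, so that it refers to worsening, that is, an increase in ODI from baseline.
2. State whether the limb applies to an arm's mean or to a proportion of patients, and what the word "significant" in it requires.
3. As a clarification, state the comparator for a higher frequency of negative neurological outcomes (the other arm or baseline), and the test or limit that decides it.

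The choice of clinical limit is the sponsor's. The cost is a wording amendment, with no extra data or patients.

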### Methods for additional analyses (e.g., subgroup analyses) {20b}

No additional analyses are planned.

### Methods in analysis to handle protocol non-adherence and any statistical methods to handle missing data {20c}

For missing outcome data, multiple imputations will be used.

### Plans to give access to the full protocol, participant level-data and statistical code {31c}

The datasets analysed during the current study and statistical code are available from the corresponding author on reasonable request, as is the full protocol.

## Oversight and monitoring

### Composition of the coordinating centre and trial steering committee {5d}

The coordinating centre is Sklifosovsky Research Institute for Emergency Medicine. The steering committee include:Chief investigator—prof. [name], MD, PhD has overall supervision of study;Researchers—[name], MD, PhD, [name], MD, PhD Responsible for recruitment, data collection, adherence to study protocol;Critical reviewer—prof. [name], MD, PhD (Burdenko Neurosurgical Center, Moscow, Russia);Independent observer—[name], MD, PhD (Pirogov National Medical and Surgical Center, Moscow, Russia). Responsible for interim analysis and auditing trial conduct.

Each clinical centre provide a local coordinator staying in direct contact with the chief investigator and the research group.

